**TND study**

V/E is calculated as 1-OR. Where OR is the odds of vaccination in cases compared to controls (SARS-CoV-2 negative).

Multivariable logistic regression will be used with adjustment for week of swab, age group, risk-status and region (or practice), at minimum. Inclusion of additional variables including sex, consultation quartile, ethnicity, IMD quintile, smoking status, EFI, large residence, Cambridge Morality Measure, and indication for swabbing (grouped as ILI / COVID-like illness, ARI or exacerbation) will be considered individually; variables that do not impact VE by more than 1% need not be included.

Vaccination status will be a categorical variable, captured at the time of swabbing: 0-13 days post dose, 14-91 days post dose, 92-182 days post dose, with separate categories for each vaccine type (or manufacturer if required). Vaccinated 6months+ ago will be the baseline category, to look at the incremental benefit of a new dose.

Primary TND analysis will impute onset status (within/beyond 10 days) where this is not given.

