**Exclusion criteria**

- Logical checks will be performed and patients identified with nonsensical records will be excluded.
- Those with unusual COVID-19 vaccine histories (vaccination outside the campaign period or receiving an alternative vaccine to the main offer – see section 3.5).
- SARS-CoV-2 negative controls with a positive influenza test will be excluded for analyses that span the main period of influenza circulation (i.e. Autumn booster evaluations, but not Spring booster evaluations).
- Patients swabbed >10 days post onset.
- Patients whose swab date cannot be determined.
- Patients with no linked vaccination history or clinical risk status.

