**3.5 Exposure**

**Definition**

All persons will be considered fully booster-vaccinated 14-days after a booster dose.

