**Outcomes for TND study of symptomatic GP visit**

TND requires both confirmed test positive cases and test negative controls to be identified. Both positive cases and negative controls should present to their GP with a defined set of symptoms, consistent with those required for participation in the sentinel swabbing scheme. Swabbing should be undertaken within ten days of onset of symptoms. Indications for swabbing include influenza-like illness, COVID19-like illness, acute respiratory infection, and asthma/COPD exacerbations.

A case is defined as an individual with a positive SARS-CoV-2 test via the sentinel swabbing scheme, with symptoms/illness within 10 days of onset.

A control is defined as an individual with a negative SARS-CoV-2 test via the sentinel swabbing scheme, with symptoms/illness within 10 days of onset AND (Autumn boosters only) influenza negative.

Multiple results may be available within any one individual, but a 90-day window between consecutive positive tests will be included in either study to ensure independence of positive outcomes.

Once timing of positive events have been established for the TND, the first negative result per 3 week period will be included, if at least 21 days before or 90 days after any positive result.

Analyses will initially exclude individuals presenting with asthma/COPD exacerbation, but indications for swabbing will be further explored in sensitivity analyses.

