**Table 1: Data sources for each collected variable**

| Group of Variables | Variables | Data source |
| --- | --- | --- |
| Demographic characteristics | Age on 31 August 2022 | Electronic GP record |
|  | Gender | Electronic GP record |
|  | GP practice ID | Electronic GP record |
|  | Location – NHS region | Electronic GP record |
|  | IMD quintile | Electronic GP record |
|  | Ethnicity | Electronic GP record |
| Exposure | COVID-19 vaccinations | Electronic GP record / linkage to NIMS |
|  | Dates of vaccinations | Electronic GP record / linkage to NIMS |
|  | Type of vaccine / manufacturer | Electronic GP record / linkage to NIMS |
|  | Batch numbers | Electronic GP record / linkage to NIMS |
| Outcomes TND only | Laboratory confirmed outcome | Linkage to PHE virus reference lab data |
|  | Date of swab | Linkage to PHE virus reference lab data |
|  | Date of onset | Linkage to PHE virus reference lab data |
|  | Date of receipt | Linkage to PHE virus reference lab data |
|  | Presence of fever ±10d | Electronic GP record |
|  | Presence of cough ±10d | Electronic GP record |
|  | Presence of shortness of breath ±10d | Electronic GP record |
|  | Consultation for ILI ±10d | Electronic GP record |
|  | Consultation for COVID19 ±10d | Electronic GP record |
|  | Consultation for URTI ±10d | Electronic GP record |
|  | Consultation for LRTI ±10d | Electronic GP record |
|  | Consultation for ARI ±10d | Electronic GP record |
|  | Consultation for Bronchitis ±10d | Electronic GP record |
|  | Consultation for Bronchiolitis ±10d | Electronic GP record |
|  | Consultation for asthma/COPD ±10d | Electronic GP record |
| Outcomes cohort only | Date of hospital admission | Linkage to HES / SUS data |
|  | Date of discharge | Linkage to HES / SUS data |
|  | List of ICD10 discharge codes | Linkage to HES / SUS data |
|  | Use of Oxygen | Linkage to HES / SUS data |
|  | Date of ICU admission | Linkage to HES / SUS data |
|  | Date of Death | Electronic GP record / linkage to ONS mortality data |
|  | Date of positive SARS-CoV-2 test | Linkage to SGSS / PHE virus reference lab data |
| Confounding factors | Smoking status | Electronic GP record |
|  | List of PRIMIS risk groups | Electronic GP record |
|  | Electronic Frailty Index | Electronic GP record |
|  | Indicator of living in a large residence | Electronic GP record (household key) |
|  | Cambridge Mortality Measure | Electronic GP record |
|  | Consultation count | Electronic GP record |

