**3.4 VE exposure**

**Definition**

Patients will be defined as vaccinated if they have received the 2022/23 seasonal vaccine at least 14 days before the date of the swab. Note that 2 doses of LAIV are recommended for some children, but will be considered vaccinated from 14 days after the first dose.

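### The COVID-19 TND counts time since dose to the swab, not to symptom onset, so some onsets before day 14 fall in the 14-91 day level; if early protection is lower, VE there is modestly diluted.

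*Protocol*

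**What the plan says.** All references are to the Protocol; no separate SAP was available.

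- **Exposure date.** Study 1, section 3.12 (TND study): "Vaccination status will be a categorical variable, captured at the time of swabbing". The levels are "0-13 days post dose, 14-91 days post dose, 92-182 days post dose".
- **Start of full status.** Section 3.5: "All persons will be considered fully booster-vaccinated 14-days after a booster dose". It does not name the event to which the 14 days are counted; section 3.12 supplies it.
- **Permitted delay.** Section 3.6 (TND outcomes): "Swabbing should be undertaken within ten days of onset of symptoms". The exclusion list in section 3.2.2 matches: "Patients swabbed >10 days post onset".
- **Onset data.** Table 1 in section 3.9 lists onset as a collected TND item: "Date of onset | Linkage to PHE virus reference lab data". In the analysis it serves only as a two-level status: "Primary TND analysis will impute onset status (within/beyond 10 days) where this is not given".
- **Study 2 (influenza).** Section 3.4 also counts to the swab: "at least 14 days before the date of the swab". Section 3.6 nevertheless uses the interval from vaccination to symptom onset when excluding recently vaccinated LAIV-eligible patients aged 2-17.

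Neither study describes an analysis that classifies general vaccination status at onset.

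**The concern.** A dose can prevent an illness only if it was given before that illness began. By keeping days 0-13 separate and starting full status at day 14, the Protocol presupposes less protection in the first two weeks. Counting to the swab partly undoes that separation, because the illness may have begun up to 10 days earlier.

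Two groups are affected. People with onset on days 4-13 can be counted as fully boosted. People vaccinated after falling ill are counted as exposed in the 0-13 day level, although that dose could not have prevented the episode. The first group matters more, because the 14-91 day level carries the main estimate of the benefit of a new dose. It also feeds a primary objective, VE by time since vaccination.

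**Working it through.** The Protocol gives no figure on this point to reproduce, so this is a range calculation.

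**From the Protocol:** exposure fixed at the swab; a 14-91 day level of 91 − 14 + 1 = 78 days; a maximum delay from onset to swab of 10 days.

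**Assumed, because not given:** delay uniform over 0-10 whole days (mean 5) and the same in cases and controls; controls spread evenly over the swab days in the level; VE before day 14 (VE_e) either zero or half of the later VE. The true VE of 50% is illustrative.

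**Step 1, who is affected.** Onset day = swab day − delay. At the maximum delay of 10 days, swab day 14 means onset on day 4, swab day 23 means day 13, and swab day 24 means day 14. So swab days 14-23 can contain onsets on days 4-13.

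**Step 2, share misplaced.** For a delay of d days, d of the 78 swab days have onset before day 14. Hence f = mean delay / 78 = 5/78 = 6.4%. This is the share among controls, which is the weight that enters the odds ratio.

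**Step 3, effect on VE.** The odds ratio in the level is (1 − f)(1 − VE) + f(1 − VE_e), so VE observed = (1 − f)·VE + f·VE_e.

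- No early protection: 0.9359 × 50% = 46.8%.
- Half protection: 0.9359 × 50% + 0.0641 × 25% = 48.4%.

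**Step 4, other assumptions (true VE 50%).**

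| Delay and accrual | f | VE_e = 0 | VE_e = half |
|---|---|---|---|
| 0-10 days, full level | 5/78 = 6.4% | 46.8% | 48.4% |
| 0-7 days, full level | 3.5/78 = 4.5% | 47.8% | 48.9% |
| 0-10 days, only days 14-60 accrued | 5/47 = 10.6% | 44.7% | 47.3% |
| All delays 10 days, full level (extreme) | 10/78 = 12.8% | 43.6% | 46.8% |

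At a true VE of 60%, the first row reads 56.2% and 58.1%.

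**Step 5, direction.** If apparent early VE were higher than later VE, for instance because people who are unwell put off vaccination, the sign changes. With VE 60% and VE_e 80%: 0.9359 × 60% + 0.0641 × 80% = 61.3%.

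**Step 6, the day 91/92 boundary.** Onsets on days 82-91 can fall in the 92-182 day level, which is 91 days wide: f = 5/91 = 5.5%. If VE is 60% before the boundary and 40% after, the later level reads 0.945 × 40% + 0.055 × 60% = 41.1%. A true drop of 20 points then appears as about 15 (56.2% to 41.1%) or 17 (58.1% to 41.1%).

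**Step 7, the 0-13 day level.** If vaccination continued at the same rate during illness, 5/14 = 36% of controls in this level would have had onset before the dose. Deferral by people who are unwell would lower this.

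**The case against.** The best defence is completeness. Swab date is known for every included record, since those without it are excluded, whereas onset is sometimes missing and its status must be imputed. Sections 3.5 and 3.12 are compatible, so a reader who infers an internal contradiction in Study 1 goes too far: this is a design weakness. The completeness argument stands as a reason to keep a swab-date analysis, but not as a reason to ignore onset dates that are held.

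Using onset where recorded and swab otherwise puts two definitions in one variable. If onset recording differs between cases and controls, that could itself bias VE. This stands, and is why both single-definition analyses are needed.

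Other stronger readings are tempting but unsupported:

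- **Infection before day 14.** Counting to onset does not remove people infected before day 14 whose symptoms began later. The claim concerns onset only.
- **The 1% rule.** Section 3.12 uses a 1% change in VE to select covariates. It is not a tolerance for misclassification.
- **The January 2024 run.** Recent doses would enlarge the effect, but the Protocol gives no distribution of dose dates. The campaign opens in September 2023, so some recipients could already be past day 91. The 14-60 day row is a scenario only.
- **Contamination by post-onset doses.** These sit in the 0-13 day level and do not enter the 14-91 day estimate.
- **The same fault in Study 2.** The case there is weaker. Section 3.5 of Study 2 aims at swabs within 0-7 days of onset, and section 3.10 fits an interaction between vaccination and that window. Section 3.8 lets contributors send only indicators at 0, 14 and 21 days in place of vaccination dates, so a dose-to-onset interval may not be derivable.

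**Conclusion.** The point holds for the COVID-19 TND. The stated rules necessarily allow onsets on days 4-13 into the 14-91 day level, and doses given after onset into the 0-13 day level. With a uniform 0-10 day delay and a fully accrued level, a true VE of 50% loses 1.6 points (half early protection) to 3.2 points (none). This is modest, but it affects the main exposure level and also tends to flatten the contrast between early and later levels.

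A reader might infer that dilution is certain. It is not: delay, early VE and true VE are all assumed, and dilution requires VE before day 14 to be lower than after. The Protocol's own levels presuppose that, but it gives no estimate. The cohort study is not affected by this wording. The change should be made because the data are already collected and the mixing is avoidable wherever onset is recorded.

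**What to change.** In Study 1, sections 3.5 and 3.12 (TND):

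1. Count time since dose from the dose to symptom onset where onset is recorded.
2. Treat a dose given after onset as not received for that episode, and classify the person on the doses received before it.
3. Use swab date only where onset is missing.
4. Report two sensitivity analyses: swab date for all records, and onset date among records with onset recorded.

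In Study 2, leave the section 3.4 definition as the main one. For adults, add the onset-based rule as a sensitivity analysis where both vaccination and onset dates are supplied.

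The cost is new wording, one derived variable and the extra runs. Some people move from the 14-91 to the 0-13 day level, and the main variable has a mixed definition where onset is missing; the two sensitivity analyses show whether that matters.

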**All studies**

Stratification by age group, risk-group, or variant period will be carried out as required. Interactions between each other factor and vaccination will be tested and if significant stratification will be considered.

Data will be analysed in Stata version 14 or 17.

**4. Limitations**

**4.1 Study population**

Representativeness: the registered practice population is representative of the national population by region, age and gender and the results of the clinical study will be generalisable to the country as a whole.

**4.2 Exposure, vaccination status**

For practical purposes in the UK, the GP record is unlikely to miss vaccination, but since vaccination will be external to the GP, recording delays are likely to occur.

**4.3 Sample size for sub-analysis**

For some stratified or sub-analyses there could be wide confidence intervals.

**4.4 Negative confounding**

These are biases reflecting that high risk groups are more likely to be vaccinated therefore reducing V/E.

This will be addressed by capturing data on risk groups. Nevertheless severity or risk factors and data quality on risk factors could still mean this is not fully measured.

Likewise, if low risk groups – in particular those who have already experienced COVID infection, are less likely to vaccinate, VE could be biased toward negative effectiveness.

This will be addressed by capturing the positive testing history, where possible, and allowing for this in the analysis. We will consider running separate analyses for those with confirmed and/or probable past infection and no history of past infection

**4.5 Positive confounding**

These are biases reflecting a healthy vaccine effect. People with a healthy behaviour and a good functional status are more likely to accept / request vaccination, therefore increasing the measured V/E.

This is not something we will be able to easily capture so is a potential limitation.

**4.6 Other potential limitations**

The comparison of V/E estimates in periods with different COVID-19 activity will allow the study to assess if the observed differences in the occurrence of the selected outcomes in vaccinated and unvaccinated are likely due to the effect of the vaccine or if they reflect baseline differences between the two groups.

Stratification by seasons or wave will be performed to assess this potential bias.

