**3.6 Outcome(s)**

**Outcomes for Cohort Studies of Severe Disease**

Linkage with ONS mortality data, Hospital Episode Statistics (HES) and/or Secondary Uses Service (SUS), should provide the following additional outcomes:

- A COVID-19 hospitalisation will be defined as hospital admission, with
  - a primary COVID-19 discharge code present. (ICD10 U07.1, U07.2, U07.4 or U07.5)
  - a primary acute respiratory code (J04, J09-J22, J80), in conjunction with BOTH a secondary COVID-19 discharge code AND a record of a positive SARS-CoV-2 test -14 to +2 days around admission (to ensure infection prior to hospitalisation)
  - consecutive admissions with the same primary code will be aggregated and the primary hospitalisations analysis will include only stays of 2 nights or longer
- Stays of any length will be evaluated in a secondary analysis
- A very severe hospitalisation definition including use of Oxygen or admission to intensive care in addition to the primary definition above will also be evaluated in a secondary analysis.
- A COVID-19 death will be defined as a death with a COVID-19 ICD10 code on the death certificate (in any position)
- A definition including additional deaths occurring within 28 days of a positive test will also be used in a secondary analysis.

Negative controls do not need to be identified.

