**Antigenic drift / emergence of new strains**

Comparisons of V/E by time period will also inform this.

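### For COVID-specific cohort outcomes, comparing VE across periods of differing COVID-19 activity cannot detect a constant baseline difference between groups, so the bias check in section 4.6 does not do what it claims

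*Protocol*

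**What the plan says.** Section 4.6 of the Protocol makes a definite claim: "The comparison of V/E estimates in periods with different COVID-19 activity will allow the study to assess if the observed differences" between the two groups "are likely due to the effect of the vaccine or if they reflect baseline differences between the two groups". It adds how this is to be done: "Stratification by seasons or wave will be performed to assess this potential bias".

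Section 4.5, just before it, describes the healthy-vaccinee effect, says that it raises measured VE, and concludes: "This is not something we will be able to easily capture so is a potential limitation". Section 4.4 describes confounding in the opposite direction.

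The next paragraph of 4.6, on antigenic drift and new strains, uses the same contrast for another purpose: "Comparisons of V/E by time period will also inform this".

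The cohort outcomes are in section 3.6. A hospitalisation needs "a primary COVID-19 discharge code present", or else a primary acute respiratory code together with both a secondary COVID-19 code and a positive test near admission. A death needs a COVID-19 code somewhere on the certificate; a secondary analysis adds deaths within 28 days of a positive test. Section 3.12 defines cohort VE as one minus a rate ratio from a Poisson model, and test-negative VE as one minus an odds ratio.

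**The concern.** Comparing busy and quiet periods is informative when the outcome includes events that the virus does not cause. With all-cause death, for example, an apparent benefit that persists when little virus circulates must be bias. The cohort outcomes here have almost no such component by design. When activity falls, events fall in both groups in proportion and the ratio does not move.

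At stake is how the results are read. Stable VE across waves is what a constant baseline difference produces, yet under section 4.6 it could be taken as evidence against one. A shift in VE is no clearer, because the Protocol also expects VE to vary with variant and with time since dose.

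**Working it through.** The Protocol gives no figure for this check, so there is none to reproduce. The claim was tested algebraically and then with numbers. Values of VE, c and b below are assumptions.

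**Inputs**
- Outcome definitions: section 3.6.
- VE scale, 1 - RR (cohort) and 1 - OR (test-negative): section 3.12.
- Activity: section 3.10 uses 15 cases per 10,000. Read as a weekly rate over 6 to 7 weeks, this gives 0.90% to 1.05%, in line with the stated 1% attack rate. It serves here only as an illustrative high level.

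**Step 1: formula.** Let L be COVID-19 activity, c the baseline rate ratio of boosted to reference people, and b a rate of non-COVID events unrelated to activity.

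Observed VE = 1 - c[L(1 - VE) + b] / (L + b)

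For a COVID-specific outcome b = 0, L cancels, and observed VE = 1 - (1 - VE)c.

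**Step 2: COVID-specific outcome.** With L at 15, 5, 1.5 and 0.15 per 10,000 per week:

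| True VE | c | Observed VE at all four levels |
|---|---|---|
| 0 | 0.6 | 1 - 1 x 0.6 = 40% |
| 20% | 0.75 | 1 - 0.8 x 0.75 = 40% |
| 40% | 1 | 1 - 0.6 x 1 = 40% |

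Pure bias, a mixture and pure effect are indistinguishable over a 100-fold range of activity.

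**Step 3: size over a range of c.**
- True VE 0: c = 0.7 gives 30%; c = 0.9 gives 10%.
- True VE 40%: c = 0.7 gives 1 - 0.6 x 0.7 = 58%; c = 0.9 gives 1 - 0.6 x 0.9 = 46%.
- c above 1 lowers observed VE in the same way, again equally in every period.

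**Step 4: where the check would work.** Take b = 15 per 10,000 per week and the same four activity levels.
- True VE 40%, c = 1: 20%, 10%, 3.6%, 0.4%.
- True VE 0, c = 0.6: 40% throughout.

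With a non-COVID component, effect and bias separate.

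**Step 5: can a change in VE be read as bias?** True VE falling from 50% to 30% with c = 1 gives observed 50% then 30%. True VE falling from 37.5% to 12.5% with c = 0.8 gives 1 - 0.625 x 0.8 = 50%, then 1 - 0.875 x 0.8 = 30%. The observed pairs are identical. Section 3.4 records several changes of dominant variant within the Autumn 2022 evaluation alone.

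**Step 6: imperfect specificity.** Suppose 2%, 5% or 10% of high-activity reference events are non-COVID and unrelated to activity, and activity falls to one fifth. An unbiased 40% VE would then move from 39.2% to 36.3%, from 38.0% to 31.7%, or from 36.0% to 25.7%. In a group of 60,000 (section 3.10 puts the smallest risk group just above this), with 50% coverage and a 0.2% attack rate (both assumed), there are 60 reference and 36 boosted events. The 95% interval around 40% is then about 9% to 60%. Incidental events that rise and fall with activity restore nothing: with 30% assumed, observed VE is again constant.

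**Step 7: test-negative design.** Here c is the ratio of the baseline difference for COVID consultations to that for other respiratory consultations. If the two are equal, c = 1 and the difference cancels from the OR. Only a COVID-specific difference would bias VE.

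**The case against.** The best case for the plan is that it does much to limit baseline differences. Frailty index, mortality measure, smoking, consultation frequency and influenza vaccination are candidate covariates. The section 3.12 baseline is people vaccinated six or more months ago, so the cohort compares previously vaccinated people with each other. Time since dose is modelled in categories, splits by variant period are planned, and a test-negative study runs alongside. Section 4.5 openly calls the healthy-vaccinee effect a limitation, and section 4.6 speaks of baseline differences generally without naming it.

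All of this stands, and it bears on how far c may lie from 1. None of it tests what remains after adjustment, and the time-since-dose and variant splits reduce but do not remove the ambiguity of a change in VE.

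A reader might infer more than the documents support:
- *That the VE estimates are wrong, or biased upward.* The Protocol gives no value for residual c, and section 4.4 describes bias in the other direction.
- *That the plan leaves healthy-vaccinee bias unaddressed.* The adjustments and baseline above are mitigation; what is lacking is a working diagnostic.
- *That the test-negative study is equally affected.* Step 7 shows that it is not.
- *That the 0-13 day category is a ready-made clean check.* The Protocol does not present it as one, and people who defer vaccination while ill would distort it.

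COVID-19 codes in any position and 28-day deaths let in some non-COVID deaths. These still need a code or a test, so they largely track activity and do not rescue the check.

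**Conclusion.** The statement in section 4.6 claims a property that the cohort design does not have. If c is constant across periods, comparing them cannot distinguish vaccine effect from a baseline difference in either direction. If c changes, the change is mixed with variant and waning. Stable VE does not rule out bias, and a shift in VE does not establish it.

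The cancellation holds for any constant c and needs no numerical assumption beyond outcome specificity and the ratio scale. The sizes in step 3 are illustrations with assumed c, not estimates of bias in this study. The planned estimates can still be produced as specified; the fault lies in the assurance attached to them.

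**What to change.** Withdraw the section 4.6 statement as a bias check, and keep stratification by season or wave for variant and waning questions.

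For the main cohort VE estimates of each campaign, fit the same Poisson model, with the same exposure categories and covariates, to two negative-control outcomes from the planned linkages:
- admissions with a non-COVID, non-respiratory primary ICD10 code (HES/SUS; Table 1 of section 3.9 already lists "List of ICD10 discharge codes");
- deaths without a COVID-19 code (ONS).

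Define admissions by diagnosis code alone, since Table 1 lists no admission-method field from which to select emergencies. Report these rate ratios beside the main VE as an indicator of residual confounding. They should not serve as a correction factor, because the baseline ratio for other causes need not equal that for COVID-19. The 0-13 day estimate may be shown as supportive only.

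The cost is two further outcomes for each of the three campaigns named in section 1, so 2 x 3 = 6 main model fits. Section 4.7 already describes the analyses as slow, so limiting this to the main estimates matters. The linkage extract must also retain non-COVID admissions.
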